## Abstract

Aging leads to changes in motor-cognitive performance. Despite the importance of physical activity for healthy aging and the need for health promotion interventions in individuals with intellectual disability (ID), there is a lack of empirically strategies for promoting health in adults with ID. Therefore, we are conducting a clinical trial (NCT06628999 on clinicaltrials.gov) to investigate a strategy for promoting healthy aging by targeting physical and cognitive domains in ID individuals. The present work aims to provide a detailed account of the study protocol of the proposed trial to promote transparency and dissemination of the ongoing research. Specifically, this project will study the effect of a vision training program on cognitive performance and physical fitness in adults with ID. A secondary aim is to examine the association between mental and physical performance outcomes. Participants will be randomly allocated into a vision training group (VT, *n* = 28), a vision training-detraining group (VTD, *n* = 28), and a control group (C, *n* = 28). During the first 8 weeks, the VT and VTD groups will follow the same training protocol (based on vision oculomotor exercises combined with postural control exercises). From weeks 9 to 16, the VT group will continue the training protocol, whereas the VTD group will abstain from training (detraining). Cognitive performance and physical fitness will be assessed at baseline, mid- and post-training intervention. Overall, a vision training program can positively impact various aspects of life for individuals with ID promoting autonomy, and social integration to counteract the aging process.

## 1 Introduction

The United Nations expects that by 2050, a fifth of the global population will be older, with 15% of the population having some form of disability (Santos et al., 2022). Healthy aging involves developing functional abilities for wellbeing in older age and encompasses physical capabilities, cognitive functioning, metabolic health and psychological wellbeing (John et al., 2023). Aging is linked to changes in the locomotor system and reduced cognitive processing, leading to deterioration in motor-cognitive performance. In this sense, research has consistently demonstrated the crucial role of physical activity in improving physical fitness and preserving cognition in healthy older individuals (Erickson et al., 2019). However, as the majority of the literature focusedon healthy aging among the general population (Wollesen et al., 2020), there is also a need to focus on wellness promotion among individuals with intellectual disabilities. While most adults with cognitive disabilities have relatively few life co-existing conditions, some of them may experience severe health issues that impact their wellbeing (Reynolds et al., 2019). Compelling evidence suggests that adults with intellectual disabilities generally face unhealthy lifestyle habits, inadequate physical activity or poor nutrition health outcomes compared to their able-bodied individuals (McGuire et al., 2007). To sum up, a better comprehension on which type of intervention could contribute to ameliorate healthier old age outcomes for adults with cognitive impairments is fundamental.

Intellectual disability (ID) represents a heterogeneous condition based on the cognitive deficit and a wide range of comorbidities with a negative impact on aging (Krahn and Fox, 2014). ID includes some genetic syndromes (e.g., Down syndrome and Fragile X syndrome) with a remarkable effect on intellectual and adaptive behavior during childhood (U.S. National Library of Medicine, 2024), leading to deficits in motor development (Belluscio et al., 2019), sensorial context (Chokron et al., 2020) and visuospatial cognition (Giuliani et al., 2011; Wilkinson and Light, 2014). Notably, vision and eye tracking play a key role in spatial orientation, stimulating several brain areas (Henderson, 2003) and people with ID display anomalous visual movements, spatial organization and cognitive performance (Giuliani et al., 2011). In addition, an earlier acquisition of essential visual functions may have a protective effect on subsequent intellectual development (Dale and Sonksen, 2002).

With this in mind, multicomponent motor-cognitive training is a promising exercise category that stimulates multiple physical and cognitive skills, showing more remarkable similarities to daily life activities. In this sense, vision training with oculomotor eye-tracking stimuli has positively affected cognitive functions (Edlin and Lyle, 2013; Formenti et al., 2019). In older people, gross–motor coordination training and cognitive tasks counter age-related cognitive decline (Forte et al., 2023). Conversely, motor-cognitive interventions can also positively affect global cognition and inhibition (Wollesen et al., 2020). A recent review analyzed current interventions to support healthy aging in individuals with ID, highlighting physical activity as a crucial factor for healthy aging while emphasizing the need for more practical health promotion strategies to enhance the wellbeing of individuals with ID (Santos et al., 2022). However, there is a paucity of literature addressing feasible strategies that target both the physical and cognitive domains in individuals with ID to counteract the age-related decline. Therefore, we are conducting an interventional randomized clinical trial to investigate a potential strategy for promoting healthy aging by targeting physical and cognitive outcomes in individuals with ID. Aim of the present work is to provide a detailed account of the study protocol of our clinical trial to promote transparency and dissemination of the ongoing research. Specifically, the proposed protocol aims to investigate the effects of a 16-week vision training programme on cognitive and motor performance in individuals with ID.

### 1.1 Study objectives

The overall main purpose of this research project is to determine the effectiveness of perceptual-vision training on cognition and physical functioning in individuals with intellectual disabilities.

Specifically, the primary endpoint is to identify the role of eye training on cognitive performance in terms of inhibitory control. The secondary endpoints are to verify the contribution of vision training on postural control, upper and lower body strength and agility outcomes. The tertiary endpoint aims to verify any potential effect of age, reinforcing the concept of promoting healthy aging.

Our primary hypothesis is that perceptual vision training intervention will promote a greater increase in cognitive and motor performance compared to the usual care control group. In addition, the secondary hypothesis is that a period of detraining could slightly attenuate the training-induced gains achieved during the previous intervention period. The third hypothesis is to detect whether there is an age-related effect on the outcomes measured.

## 2 Material and methods

This study was approved by the University of Insubria Ethics Committee (protocol number 0119168, date 12.03.2024) and registered in ClinicalTrials.gov (NCT06628999) in compliance with the Helsinki Declaration. Written informed consent will be obtained from patients following the tenets of the Declaration of Helsinki on studies with human participants (Holt, 2014).

### 2.1 Study population

Participants will be recruited from local communities dwelling in Northern Italy. The inclusion criteria include age between 40 and 70 years with a low-to-mild intellectual disability (Intellectual Quotient, IQ = 51–69) defined with the Wechsler Scale of Intelligence (WAIS-IV), a scale particularly suited for individuals with an age range from 16 to 90 years composed by four sub-tests that would provide a comprehensive general intelligence index. The exclusion criteria are (a) inability to understand essential verbal communication, (b) strict dependence on personnel or assistive support devices, (c) presence of concomitant sensorial or physical impairments and (d) presence of behavioral problems or any other clinical condition that may compromise the practice of regular physical activity.

### 2.2 Study design

This project is a three-arm, parallel, randomized controlled trial. In detail, Figure 1 highlights the flow diagram of the overall design setting. At the beginning, participants will have their body mass and height measured. After that, a 1-week familiarization period will be implemented during which participants will adapt to the exercise techniques used throughout the study. Following 1 week of baseline testing, participants will be randomly assigned to three groups: (i) a Visual Training Group (VT, *n* = 28) that will perform oculomotor exercises combined with postural control exercises (Formenti et al., 2019) for 16 weeks; (ii) a Visual Training-Detraining group (VTD, *n* = 28) that will follow the same training protocol of VT for the first 8 weeks, abstaining from any training for the following 8-weeks period (from week 9 to week 16) and (iii) a control group (C, *n* = 28) in which no intervention will be implemented. Randomization will be achieved using a random-number generator (https://www.random.org using a 1:1:1 ratio) and to ensure adequate allocation concealment this procedure will be carried out by a blinded external researcher. An independent researcher will conduct the allocation sequence until the interventions are assigned. A research team collaborator will enroll and assign participants to the three groups. Baseline testing will be repeated after 8 weeks (mid-training testing) and at the end of week 16 (post-training testing).

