### 2.3 Intervention protocol

The intervention programs for VT and VTD groups will be performed using the premium equipment of the S.V.T.A. training kit (S.V.T.A. method©, Carmagnola, Italy). This method combines visual skills (e.g., peripheral vision, saccadic eye movements, accommodation and vergence skills) with postural control actions. Each training session will be structured in a circuit-training format composed of 5 stations in which participants will perform the prescribed exercises for 6 min. Each station will be characterized by different panels fixed on a wall about 1.5 m from ground level, with colors, letters, and numbers as targets. VT and VTD groups will perform the same motor-cognitive oculomotor training combined with postural control exercises structured in four incremental sub-phases, as proposed by Formenti et al. (2019): phase 1 (weeks 1–4), phase 2 (weeks 5–8), phase 3 (weeks 9–12) and phase 4 (weeks 13–16). The difficulty of the oculomotor task increases progressively from Phase 1 to Phase 4 (for example, from bipedalism to monopodial stance and from close to far). The training circuit is composed of 5 stations (represented in Figure 2):

*Station 1*. A square board with nine points on a wall. Participants must move their gaze on external points in clockwise and anticlockwise directions, maintaining their focus on the central point.

*Station 2*. A rectangular board with an infinity profile on a wall. The infinity profile comprises a sequence of randomized red and blue points. Participants have to move their gaze from one point to another following the infinity profile while pronouncing the color of the point identified.

*Station 3*. A square board of four circles formed by a random sequence of red and blue letters fixed on a wall. Participants must move their gaze from one letter to another while pronouncing the identified one, maintaining the visual focus on the central point.

*Station 4*. A square board of 81 cells is fixed on the wall. Red or blue cells contain a random number from 0 to 9. Each participant holds a board comprising an image like the one on the wall. Participants have to read the numerical digit on the board in their hands and localize the same numerical digit on the board on the wall.

*Station 5*. Two boards with black-colored numerical digits (0 to 9) are fixed vertically on the wall. Participants must read digits while shifting their gaze from one board to another in mediolateral and sagittal directions.

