### 2.5 Statistical analysis

The sample-size calculation is established based on a previous study (Formenti et al., 2019) on the primary outcome (incongruent condition of the Flanker task) using G^*^Power software. From a priori power analysis, observing a sample size of up to 84 individuals (β = 0.9) is requested, respecting a large effect size (Cohen's f equal to 0.4) with a type I error rate of α = 0.05. All data will be presented as mean ± standard deviation. The dataset will be tested for normal distribution using Shapiro–Wilk's normality test. Based on the study's design, the primary independent endpoints are the treatment groups and time. A two-way (treatment × time) repeated measures ANOVA will be used on each outcome variable to determine the interaction between the three time points (baseline, 8 weeks, 16 weeks) and groups (VT, VTD, C). If an interaction exists, the simple effect and pairwise comparisons will detect differences between groups at each time point. Subsequently an additional age stratification and comparison will be performed to check any age-related difference. If a main effect is detected, data will be analyzed using a *post-hoc* analysis (Bonferroni test). The significance level will be set at *p* < 0.05. Partial eta squared (Part 2) effect size will be used to estimate the magnitude of the difference within each group, respecting a threshold for small (0.01), moderate (0.06) and large effects (0.14) (Cohen, 2013).

If the Shapiro-Wilk's normality test is not passed, non-parametric tests will be applied. The Friedman Test will be performed to detect differences between groups over time in both primary and secondary outcomes. In addition, to examine where the differences occur, a Wilcoxon Signed Rank test with Bonferroni adjustment will be used as a *post-hoc* analysis. Also, in these tests, the significance level will be set at *p* < 0.05.

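### Age is expected to change the cognitive gain and is the tertiary endpoint, yet it is absent from the stated main model and from the described allocation

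*Protocol article*

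**What the plan says.** All places are in the protocol article.

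- **Design and allocation (2.2).** "This project is a three-arm, parallel, randomized controlled trial". The tool and ratio are given: "Randomization will be achieved using a random-number generator (https://www.random.org using a 1:1:1 ratio"). An external researcher and concealment are mentioned, and each arm is set at 28. No stratum, block or minimisation factor is named.
- **Age range (2.1).** "The inclusion criteria include age between 40 and 70 years".
- **Role of age (1.1 and 3).** The age effect is the tertiary endpoint and the third hypothesis. Section 3 expects older participants to benefit less on cognition than younger ones.
- **Analysis (2.5).** Each outcome gets a two-way repeated measures ANOVA with treatment and time as its only factors. Age follows as a separate step: "Subsequently an additional age stratification and comparison will be performed to check any age-related difference". The non-parametric fallback (Friedman and Wilcoxon tests) has no age term either.
- **Recruitment and delivery (2.1, 2.3).** "Participants will be recruited from local communities dwelling in Northern Italy". "Each training session will be structured in a circuit-training format composed of 5 stations". The number and size of communities, the number of people per session and the number of trainers are not given. The comparator is "a control group (C, *n* = 28) in which no intervention will be implemented".

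**The concern.** The plan predicts that age affects how much people change over the 16 weeks, at least on cognition, where its primary outcome lies. A factor expected to affect the change score is worth balancing at allocation and worth modelling. The article describes neither for the main comparison.

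The distinction between level and change matters. The planned test is the treatment × time interaction. A stable difference in level between older and younger people falls in the between-subject part of that analysis and does little harm. An age-related difference in gain does not cancel. It adds to the error of the interaction, and any age imbalance between arms shifts the contrast. Level differences also re-enter in the follow-up comparisons of groups at each time point.

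At stake are the precision of the main contrast, the ease of interpreting it if the arms happen to differ in age, and the quality of the age comparison the plan wants to make.

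**Working it through.** **The plan's own figure.** Total 84, three groups, f = 0.4, α = 0.05, and 0.9 (labelled β, read here as power). For a one-way ANOVA, λ = N·f² = 84 × 0.16 = 13.44 with 2 and 81 degrees of freedom. Power is 0.907, and the smallest total with equal arms is 84, so the figure reproduces. Stratifying by age does not itself change it.

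**Chance imbalance in age.** Inputs: arms fixed at 28 (section 2.2), and 42 of the 84 counted as older (assumed, because the article gives no age bands). The numbers of older participants per arm then follow a multivariate hypergeometric distribution.

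- For one given pair, the variance of the difference is 2 × 28 × 0.5 × 0.5 × 84/83 = 14.17, so SD = 3.76.
- Normal check with continuity correction for a gap of 6 or more: 5.5/3.76 = 1.46, giving a two-sided probability of about 14%.
- Exact enumeration:

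| Gap in older participants | One given pair (e.g. VT vs C) | Largest gap among the three arms |
|---|---|---|
| 6 or more of 28 | 14% | 30% |
| 8 or more of 28 | 4.5% | 12% |

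**What a gap does to the contrast.** Suppose older and younger people differ by d in mean change, equally in all arms. A gap of 6 of 28 moves the between-arm difference in change by (6/28) × d = 0.21 d. The article gives no value for d, so the effect on the Flanker outcome cannot be stated.

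**Community.** With individual randomisation and community left out of the analysis, simulated type I error of an ANOVA on one score per person stays at 0.049 to 0.051 for community ICCs of 0 to 0.20 (4 or 7 equal communities assumed). When allocation is stratified by community but the analysis leaves it out, it falls to about 0.03 to 0.04 for ICCs of 0.05 to 0.20. A factor used in allocation should therefore stay in the model.

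**Training groups (conditional).** Group size m and ICC are both assumed. Controls are taken as unclustered and training groups as arm-specific. Design effect DE = 1 + (m − 1)·ICC. The variance ratio is (DE + 1)/2 for VT vs C and DE for VT vs VTD. Type I error = 2(1 − Φ(1.96/√ratio)).

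| m | ICC | DE | VT vs C | VT vs VTD |
|---|---|---|---|---|
| 5 | 0.02 | 1.08 | 5.5% | 5.9% |
| 5 | 0.10 | 1.40 | 7.4% | 9.8% |
| 14 | 0.02 | 1.26 | 6.5% | 8.1% |
| 14 | 0.10 | 2.30 | 12.7% | 19.6% |

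If VT and VTD participants train in the same sessions, simulated type I error for VT vs VTD is about 0.05 (0.049 to 0.056) for the same group sizes and ICCs.

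**The case against.** The strongest reply is that this is an article condensing a fuller protocol, and blocking or stratification details are commonly left to that document. That stands for the allocation: silence here does not show that none is planned. It does not answer the analysis point, because section 2.5 states the main model and its two factors outright and places age afterwards.

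A second reply is that randomisation already covers chance imbalance. It does: the nominal α allows for it, and nothing here is bias. The 30% figure is also the worst of three pairs; for one pre-specified pair it is 14%. What remains is a loss of precision that can be avoided at almost no cost.

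Three stronger readings are tempting, and the documents do not support them.

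- A reader might infer that allocation is a simple, wholly unrestricted draw. The text does not say so. Simple randomisation of 84 people gives exactly 28/28/28 only about 1% of the time, so the fixed arm sizes point to some restriction on totals.
- A reader might infer that recruiting from several communities makes standard errors too small. With individual randomisation it does not, as the simulation shows. The wording in section 2.1 may also simply mean people living in the community rather than discrete sites.
- A reader might infer from the circuit format that participants train together in groups and that error rates are seriously inflated. Group delivery is plausible but not stated. The 19.6% value needs arm-specific groups of 14 and an ICC of 0.10, none of which is in the article.

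**Conclusion.** The point holds for age. The plan makes age an endpoint and expects it to change the cognitive gain, but leaves it out of the stated model and names no balancing on it. Under an assumed 42/42 split, a gap of 6 or more older participants between some two arms has a chance of about 30% (14% for a given pair). The consequence is lost precision and a harder interpretation, not bias. Its size on the outcome depends on an age difference in change that the article does not give.

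Clustering by training group is a conditional point only. It matters if sessions are arm-specific, to a degree set by an unstated group size and ICC, and essentially not at all for VT vs VTD if those arms share sessions. Community is not a threat to the error rate. At most it is a candidate covariate.

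**What to change.** 1. **Model.** Pre-specify age and age × time as covariate terms in the model for every outcome. Say how age will be handled if the non-parametric fallback is used, since those tests as described take no covariate. The later age comparison can remain as the tertiary analysis.
2. **Allocation.** For participants not yet allocated, randomise within age band in small concealed blocks, generated by the same external researcher, and keep the age term in the model.
3. **Community.** Add recruiting community as a further model term only if there are a few discrete communities.
4. **Training groups.** State whether sessions are shared and whether VT and VTD train together. If groups are arm-specific, record each trained participant's group and report a sensitivity analysis that allows for clustering in the trained arms, with a small-cluster correction. Groups of 14 would leave 28/14 = 2 clusters per arm, where an ordinary random effect or robust standard error is unreliable, so this should not replace the main analysis.

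The cost is one allocation list per age band, a few degrees of freedom, arm sizes that may differ from 28 by one or two and, for item 4, one extra recorded variable. Age is already needed for eligibility, so items 1 and 2 call for no new data.

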**Figure 1 F1:**
[figure not shown]
CONSORT diagram of the research.

### 2.3 Intervention protocol

The intervention programs for VT and VTD groups will be performed using the premium equipment of the S.V.T.A. training kit (S.V.T.A. method©, Carmagnola, Italy). This method combines visual skills (e.g., peripheral vision, saccadic eye movements, accommodation and vergence skills) with postural control actions. Each training session will be structured in a circuit-training format composed of 5 stations in which participants will perform the prescribed exercises for 6 min. Each station will be characterized by different panels fixed on a wall about 1.5 m from ground level, with colors, letters, and numbers as targets. VT and VTD groups will perform the same motor-cognitive oculomotor training combined with postural control exercises structured in four incremental sub-phases, as proposed by Formenti et al. (2019): phase 1 (weeks 1–4), phase 2 (weeks 5–8), phase 3 (weeks 9–12) and phase 4 (weeks 13–16). The difficulty of the oculomotor task increases progressively from Phase 1 to Phase 4 (for example, from bipedalism to monopodial stance and from close to far). The training circuit is composed of 5 stations (represented in Figure 2):

*Station 1*. A square board with nine points on a wall. Participants must move their gaze on external points in clockwise and anticlockwise directions, maintaining their focus on the central point.

*Station 2*. A rectangular board with an infinity profile on a wall. The infinity profile comprises a sequence of randomized red and blue points. Participants have to move their gaze from one point to another following the infinity profile while pronouncing the color of the point identified.

*Station 3*. A square board of four circles formed by a random sequence of red and blue letters fixed on a wall. Participants must move their gaze from one letter to another while pronouncing the identified one, maintaining the visual focus on the central point.

*Station 4*. A square board of 81 cells is fixed on the wall. Red or blue cells contain a random number from 0 to 9. Each participant holds a board comprising an image like the one on the wall. Participants have to read the numerical digit on the board in their hands and localize the same numerical digit on the board on the wall.

*Station 5*. Two boards with black-colored numerical digits (0 to 9) are fixed vertically on the wall. Participants must read digits while shifting their gaze from one board to another in mediolateral and sagittal directions.

